**Figure 2 F2:**
[figure not shown]
**Schematic overview of the administration system for ^166^Ho-RE**.The administration system consists of the following components: iodine contrast agent (Visipaque ^®^, GE Healthcare) (1), saline solution (2), 20-ml syringe (Luer-Lock) (3), three-stopcock manifold (4), one-way valve (5), inlet line (6), administration vial containing the ^166^Ho-PLLA-MS (7), outlet line (8), flushing line (9), Y-connector (10) and catheter (11).

**Table 2 T2:** Dose (Gy) and activity (MBq) relation of ^166^Ho treatment

	Liver weight (kg)				
	1	1,5	2	2,5	3
Liver dose (Gy)	A (MBq)	A (MBq)	A (MBq)	A (MBq)	A (MBq)

10	630	945	1260	1575	1890
**20**	**1260**	**1890**	**2520**	**3150**	**3780**
30	1890	2835	3780	4725	5670
**40**	**2520**	**3780**	**5040**	**6300**	**7560**
50	3150	4725	6300	7875	9450
**60**	**3780**	**5670**	**7560**	**9450**	**11340**
70	4410	6615	8820	11025	13230
**80**	**5040**	**7560**	**10080**	**12600**	**15120**

In bold: the four consecutive cohorts receive 1.3 GBq/kg (20 Gy), 2.5 GBq/kg (40 Gy), 3.8 GBq/kg (60 Gy) and 5.0 GBq/kg (80 Gy), respectively. As an example, a patient in the first cohort (20 Gy) with a 1.5-kg liver, will be administered a total activity of 1890 MBq

where LW is the liver weight of the patient which may be determined using CT, MRI or ultrasound, and where 15.87 × 10 ^-3 ^(J/MBq) is the activity-to-dose conversion factor for ^166^Ho [23].

### Radiation exposure rate

During the hospitalization in week 1 the radiation exposure rate will be measured from 1 m distance at t = 0, 3, 6, 24, and 48 hours following ^166^Ho-PLLA-MS administration. Patients will not be discharged from the hospital until the dose equivalent is less than 90 μSv/h measured from 1 m distance.

### Follow-up

All patients are followed over a period of 12 weeks after treatment with weekly visits at the outpatient clinic. During each visit, data is collected by physical examination, WHO performance status assessment and laboratory examination (haematology, coagulation profile, serum chemistry and (if applicable) tumour marker). Adverse events are monitored. In addition, patients are asked to fill out the EORTC questionnaires in the 6 ^th ^and 12 ^th ^week post-treatment. CT and (in case of ^18^F-FDG-avid tumours) PET are performed in the 6 ^th ^and 12 ^th ^week post-treatment and MRI is performed in the 1 ^st ^and the 12 ^th ^week post-treatment (Figure 3).

**Figure 3 F3:**
[figure not shown]
**Timeline for study participants**. *only in ^18^F-FDG-avid tumours.

#### Holmium content

Pooled urine samples will be collected from 0-3 hours, 3-6 hours, 6-24 hours and 24-48 hours post- ^166^Ho-PLLA-MS administration. In the 6 ^th ^and 12 ^th ^week post treatment, pooled 24-hours urine will be collected for measurement of holmium content. The date and time of the start and the end of the collection period, the volume and whether the collection was complete or not, will be noted in the case record form. During the hospitalization in week 1, blood will be drawn for measuring the holmium content in the blood at t = 0, 3, 6, 24, and 48 hours following ^166^Ho-PLLA-MS administration. Measurements will be done according to activity measurement of holmium-166 metastable ( ^166m^Ho, T _1/2 _≈ 1200 year) with a low-background gamma-counter (Tobor, Nuclear Chicago, Chicago, IL, USA) as previously described in one of the preclinical studies by Zielhuis *et al*. [19].

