### Medical device

Using the solvent evaporation technique, non-radioactive holmium-165 ( ^165^Ho) and its acetylacetonate complex (HoAcAc) can be incorporated into the poly(L-lactic acid) matrix to form microspheres (Figure 1). Subsequently, the non-radioactive ^165^Ho-PLLA-MS can be made radioactive by neutron activation in a nuclear facility and form ^166^Ho-PLLA-MS. Neutron-activated ^166^Ho has a half-life of 26.8 hours and is a beta emitter (E_βmax _= 1.85 MeV) that also emits gamma photons (E_γ _= 81 keV) suitable for single photon emission computed tomography (SPECT) (Table 1).

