### Treatment

#### ^166^Ho-PLLA-MS treatment dose

When the amount of lung shunting does not exceed 20% of the safety dose of ^166^HoPLLA-MS, the (complete) treatment dose of ^166^HoPLLA-MS will be administered (Figure 2). Consecutive cohorts of 3 patients will be treated with identical amounts of microspheres (600 mg), and the last cohort will consist of at least 6 patients. If no toxicity ≥ grade 3 according to the Common Terminology Criteria for Adverse Events (CTCAE)[26] is observed, the next cohort of three patients will be treated at the next radiation dose level. If in one patient CTCAE ≥ grade 3 is observed in a particular cohort, the cohort will be extended to six patients. If toxicity ≥ grade 3 is observed in two or more patients in a particular cohort, the study will be terminated because the endpoint, e.g. the maximum tolerated radiation dose, is reached. This will be reported to the Independent Ethics Committee (IEC). The dose level prior to the toxic radiation dose will become the recommended dose for efficacy studies. If an event is classified as grade 3 or 4 administration technique related, the patient will be replaced. The specific activity of the ^166^Ho-PLLA-MS will be increased by adapting the activation time in the nuclear reactor. The first, second, third and fourth cohort will be treated with a dose of 1.3, 2.5, 3.8 and 5.0 GBq/kg (liver weight), respectively. Assuming a homogenous uptake throughout the liver, this equals escalating radiation doses of 20 Gy, 40 Gy and 60 Gy, to a maximum dose of 80 Gy in the last cohort. A maximum of 15.1 GBq will be given to the maximum treated liver weight (inclusive the tumour tissue) of 3 kg (Table 2). The amount of radioactivity administered to the patient is calculated according to the following formula:

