### Secondary objectives

Secondary objectives are to evaluate tumour response, performance status, biodistribution, quality of life and to compare the accuracy of the ^99m^Tc-MAA scout dose with a safety dose of ^166^Ho-PLLA-MS, in predicting microsphere distribution of the treatment dose. Tumour response will be quantified using CT of the liver scored according to Response Evaluation Criteria in Solid Tumours guidelines (RECIST 1.1) [27]. Tumour viability will be assessed by PET, depending on tumour type. In addition, the antitumoral effect will be assessed by relevant tumour markers responses if applicable (i.e. carcinoembryonic antigen (CEA) in colorectal carcinoma and chromogranin A (CgA) for neuroendocrine tumours). Biodistribution is assessed using quantitative SPECT and MRI. Urine and blood samples will be screened for presence of ^166^Ho-PLLA-MS or fragments of ^166^Ho-PLLA-MS. Performance status is assessed using WHO performance status criteria. Quality of life (QoL) is evaluated using the EORTC questionnaire QLQ-C30 with colorectal liver metastases module QLQ-LMC21. Finally, the accuracy of the ^166^Ho-PLLA-MS safety dose in predicting the distribution of the treatment dose is compared with the accuracy of the ^99m^Tc-MAA. Quantitative SPECT analysis will be performed using the scatter correction method described by De Wit *et al*. [14].

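### Holmium in the 0-48 h blood and urine samples is measured through the long-lived isomer 166mHo alone, so the blood screen has low sensitivity to small releases

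*Protocol article*

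**What the plan says.** Protocol article, Follow-up, Holmium content, sets the sampling schedule and the assay.

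- Blood: "blood will be drawn for measuring the holmium content in the blood at t = 0, 3, 6, 24, and 48 hours following" administration.
- Early urine: "Pooled urine samples will be collected from 0-3 hours, 3-6 hours, 6-24 hours and 24-48 hours post" administration.
- Late urine, in weeks 6 and 12: "pooled 24-hours urine will be collected for measurement of holmium content".
- Assay: "Measurements will be done according to activity measurement of holmium-166 metastable", half-life about 1200 years, in a low-background gamma-counter, with reference to a preclinical study. No sample is exempted and no other nuclide is named.

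The section Medical device says that 166Ho "has a half-life of 26.8 hours" and emits an 81 keV gamma photon. Secondary objectives gives the purpose of the samples: "Urine and blood samples will be screened for presence of" microspheres or their fragments.

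**The concern.** The isomer is needed only once 166Ho has decayed away, which applies to the week-6 and week-12 urine. No blood sample is taken that late. For the blood and early urine, the stated method leaves unused the much stronger signal that the same tube contains, and relies on one that is weaker by several orders of magnitude.

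This is a first clinical study of the device. The Discussion treats the absence of significant radionuclide release as part of the analogy with 90Y microspheres, and the blood and urine samples are a direct check of that in patients. If the assay can see only fairly large releases, a series of negative blood results would support the premise less than it appears to.

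**Working it through.** **Inputs from the article.** Half-life 26.8 h for 166Ho (Medical device) and about 1200 years for 166mHo (Holmium content). Conversion factor 15.87 × 10^-3 J/MBq, and Table 2 activities from 1260 MBq (20 Gy, 1 kg) to 15120 MBq (80 Gy, 3 kg).

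**Assumptions, because the article gives no figures.** Ratio r of 166mHo to 166Ho atoms at administration: 1, 0.05 or 0.01. Blood volume 5 L, sample 10 mL, released holmium evenly mixed in blood. Detection limit 0.1 Bq, varied below.

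**Step 1. The plan's own activities.** A = dose × liver weight / 0.01587.
- 80 × 3 / 0.01587 = 15123 MBq (Table 2: 15120).
- 20 × 1 / 0.01587 = 1260 MBq (Table 2: 1260).

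**Step 2. 166Ho remaining.** 2^(-t/26.8) gives 100% at 0 h, 54% at 24 h, 29% at 48 h, and 4.8 × 10^-12 at week 6 (1008 h, 37.6 half-lives).

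**Step 3. Activity ratio, 166Ho to 166mHo.** Ratio = (1200 × 8766 h / 26.8 h) × 2^(-t/26.8) / r = 392,507 × 2^(-t/26.8) / r.
- r = 1: 3.9 × 10^5 at 0 h, 2.1 × 10^5 at 24 h, 1.1 × 10^5 at 48 h.
- r = 0.05: 7.9 × 10^6 at 0 h, 2.3 × 10^6 at 48 h.
- Week 6, r = 1: 1.9 × 10^-6, so only the isomer can be counted.

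These are ratios of decays. Photons per decay and counter efficiency are not given. If, for illustration, the isomer yielded 100 times more counts per decay, the 48 h ratio at r = 1 would still be about 1.1 × 10^3.

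**Step 4. Isomer activity in a blood sample.** Total 166mHo = A × r / 392,507. At r = 1 this is 38,522 Bq for 15120 MBq and 3,210 Bq for 1260 MBq. A 10 mL sample holds 10/5000 = 0.002 of what is in the blood, so complete release would give 77.0 Bq and 6.42 Bq respectively, multiplied by r.

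**Step 5. Smallest detectable release** = detection limit / (sample activity at complete release).

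| Activity | Limit | r = 1 | r = 0.05 | r = 0.01 |
|---|---|---|---|---|
| 15120 MBq | 0.05 Bq | 0.065% | 1.3% | 6.5% |
| 15120 MBq | 0.1 Bq | 0.13% | 2.6% | 13% |
| 15120 MBq | 1 Bq | 1.3% | 26% | unreachable |
| 1260 MBq | 0.05 Bq | 0.78% | 16% | 78% |
| 1260 MBq | 0.1 Bq | 1.6% | 31% | unreachable |
| 1260 MBq | 1 Bq | 16% | unreachable | unreachable |

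**Step 6. The same sample counted for 166Ho.** A 0.1% release gives, at 48 h, 15120 × 10^6 × 0.001 × 0.002 × 0.289 = about 8,700 Bq, and about 730 Bq at 1260 MBq. The isomer in those samples is 0.077, 0.0039 or 0.0008 Bq at 15120 MBq for the three values of r, and 12 times less at 1260 MBq. If the 48 h sample is counted three days later (120 h, 4.5% remaining), the lowest activity still leaves 2520 × 0.045 = about 113 Bq of 166Ho.

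**Step 7. Urine.** If a whole pooled collection were counted, a 1% release would give 385, 19 or 3.9 Bq of isomer at 15120 MBq and 32, 1.6 or 0.32 Bq at 1260 MBq.

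**The case against.** **A journal article condenses the protocol.** Counting time, sample volume, calibration and detection limit may well be fixed elsewhere, and the cited preclinical method is not at hand. This stands: their absence is not the point. The nuclide, however, is stated positively and for all samples, and that choice is what is questioned.

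**Weak relative to 166Ho does not mean undetectable.** This also stands. A reader might infer that blood results will be negative whatever is released. The article does not support that, because it gives no detection limit. Under the assumptions above, a large release at the higher activities would be seen, and pooled urine contains more isomer in total than a blood aliquot.

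**The direction of error depends on when samples are counted.** If they were counted at once without energy discrimination, residual 166Ho would raise the reading. If they were stored, the two activities become equal only after about 21 days (r = 1) to 28 days (r = 0.01); beyond that the isomer is the coherent marker. Storage is a workable plan, but it gives up the strong signal.

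**Dose level.** Because specific activity "will be increased by adapting the activation time in the nuclear reactor" while the mass stays at 600 mg, a reader might infer that trends over cohorts are confounded by the choice of isomer. That does not follow. The 12-fold span in Table 2 (15120/1260) applies equally to 166Ho activity per mg, so it does not distinguish the two markers, and the article announces no test of a trend.

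**Limited importance.** Biodistribution is assessed mainly by SPECT and MRI, and blood and urine screening does not enter the escalation rule. Both are true and limit the weight of the point.

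**Conclusion.** The point holds as one of sensitivity. For the 0-48 h samples the article names only 166mHo, when 166Ho is between 3.9 × 10^5 (0 h) and 1.1 × 10^5 (48 h) times more active at r = 1, and more so if the isomer is the minority product. The factor of at least about 10^5 rests on the two stated half-lives and on isomer atoms not exceeding 166Ho atoms, which the article does not state. The detectable-release figures rest further on the assumed limit, volumes and mixing; they show the order of magnitude and are not predictions.

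On those assumptions, a negative blood result leaves open releases from about a tenth of a percent up to tens of percent of the dose, depending on administered activity and isomer share. That weakens the screening listed under the secondary objectives. It does not mean that every blood result must be negative, and it does not touch dose escalation or the maximum tolerated dose.

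**What to change.** In Holmium content, split the assay by sampling time:

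- Count the 0-48 h blood and urine samples for 166Ho within a few days of collection, decay-correct to the sampling time, and express the result as a percentage of administered activity.
- Keep 166mHo for the week-6 and week-12 urine, where 166Ho has decayed.
- Report the detection limit as a percentage of administered holmium, so that a negative result can be interpreted.

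The samples stay the same, and so does the type of counter. The cost is logistic: early samples must be handled and counted promptly while still radioactive, with dilution if the count rate is too high.

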### Primary objective

The primary objective of this study is to establish the safety and toxicity profile of treatment with ^166^Ho-PLLA-MS. This profile will be established using the CTCAE v3.0 methodology and will be used to determine the maximum tolerated radiation dose. Any of the following events which are considered possibly or probably related to the administration of ^166^Ho-PLLA-MS will be considered a serious adverse event during the 12 weeks follow-up period:

• Grade 3-4 neutropenic infection (absolute neutrophil count < 1.0 × 10 ^9^/L) with fever > 38.3°C,

• Grade 4 neutropenia lasting > 7 days,

• Grade 4 thrombocytopenia (platelet count < 25.0 ×10 ^9^/L),

• Grade 3 thrombocytopenia lasting for > 7 days,

• Any other grade 3 or 4 toxicity (excluding expected AST/SGOT, ALT/SGPT elevation, elevated bilirubin and lymphopenia) possibly related to study device, using CTCAE v3.0.

• Any life threatening event possibly related to the study device: events as a consequence of inadvertent delivery of ^166^Ho-PLLA-MS into non-target organs like the lung (radiation pneumonitis), the stomach and duodenum (gastric/duodenal ulcer or perforation), the pancreas (radiation pancreatitis), and liver toxicity due to an excessive radiation dose ("radiation induced liver disease" (RILD) [10]).

The haematological and biochemical adverse events as well as RILD will be considered dose limiting toxicity.

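### The protocol does not fix consistently whether a short or afebrile cytopenia is dose limiting

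*Protocol article*

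**What the plan says.** The Primary objective section of the protocol article states that the CTCAE v3.0 toxicity profile will serve to determine the maximum tolerated radiation dose. It then lists events, possibly or probably related to the microspheres, each of which "will be considered a serious adverse event during the 12 weeks follow-up period". The lines that bear on blood counts are:

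- Line 1: "Grade 3-4 neutropenic infection", with a neutrophil threshold and fever above 38.3°C.
- Line 2: "Grade 4 neutropenia lasting > 7 days".
- Line 3: "Grade 4 thrombocytopenia (platelet count < 25.0" × 10⁹/L), at any duration.
- Line 4: "Grade 3 thrombocytopenia lasting for > 7 days".
- Line 5, the catch-all: "Any other grade 3 or 4 toxicity (excluding expected AST/SGOT, ALT/SGPT elevation, elevated bilirubin and lymphopenia) possibly related to study device".

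After the list comes a separate sentence: "The haematological and biochemical adverse events as well as RILD will be considered dose limiting toxicity".

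The escalation rule stands elsewhere, under the heading on the treatment dose. If no toxicity of CTCAE grade 3 or higher "is observed, the next cohort of three patients will be treated at the next radiation dose level". One patient with such toxicity extends the cohort to six, and two or more end the study, with the previous dose level becoming the recommended one. This rule has no duration or fever limit and does not refer to the list.

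**The concern.** Lines 1, 2 and 4 set limits on which cytopenias count. Line 5 then counts other grade 3 or 4 toxicity and removes only expected AST/ALT elevation, elevated bilirubin and lymphopenia. A three-day grade 4 neutropenia meets none of lines 1 to 4, but it is a grade 4 toxicity that line 5 does not exclude. Whether it counts depends on whether *other* means other events than those defined above or other types of toxicity.

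The next two steps do not settle this. The closing sentence does not say whether its haematological events are those of lines 1 to 4 or also any that enter through line 5. The escalation rule uses a third, wider definition.

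At stake is the primary result. In a 3+3 scheme, one event expands a cohort and a second ends the study and fixes the recommended dose. If the event definition allows two answers for one patient, the maximum tolerated dose can depend on which answer is taken.

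**Working it through.** **1. Sample size, for orientation.** Three cohorts of 3 plus a last cohort of 6 give 3×3 + 6 = 15. Four cohorts of 6 give 4×6 = 24. The stated 15 to 24 reproduces and does not depend on this point.

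**2. Hypothetical patients put through the text.**

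| Event | Lines 1–4 | Line 5, *other* = other types | Line 5, *other* = other events | Escalation rule as written |
|---|---|---|---|---|
| Grade 4 neutropenia, 3 days, no fever | no | no | yes | counts |
| Grade 3 neutropenia, no fever or infection | no | no | yes | counts |
| Grade 3 thrombocytopenia, 4 days | no | no | yes | counts |
| Grade 4 thrombocytopenia, 4 days | yes (line 3) | not needed | not needed | counts |
| Grade 3 lymphopenia | no | no (excluded) | no (excluded) | counts |

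The first three rows are open within the list. The fourth is not, because grade 4 thrombocytopenia has no duration limit. The last column shows a wider mismatch: the escalation rule also counts events that the list excludes by name.

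**3. Illustrative effect on stopping.** The documents give no event rates, so every rate here is an assumption. Let p be a constant, independent risk per patient of a counted event, and q = 1 − p. Under the stated rule:

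- P(clear one of the first three levels) = q³ + 3pq²·q³
- P(clear the last cohort of 6) = q⁶ + 6pq⁵
- P(stop before 80 Gy is cleared) = 1 − [P(clear a level)]³ × P(clear the last cohort)

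Take a 5% risk of events that count on any reading, and let counted short cytopenias add an independent risk s, so that p = 1 − 0.95(1 − s).

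| s | p | Clear one level | Cubed | Clear last cohort | P(stop) |
|---|---|---|---|---|---|
| 0 | 0.0500 | 0.9734 | 0.9224 | 0.9672 | 0.108 |
| 0.02 | 0.0690 | 0.9517 | 0.8621 | 0.9407 | 0.189 |
| 0.05 | 0.0975 | 0.9102 | 0.7541 | 0.8906 | 0.328 |
| 0.10 | 0.1450 | 0.8238 | 0.5590 | 0.7882 | 0.559 |

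With a 10% base risk, the chance of stopping at a single 3+3 level is 9.4% if short cytopenias do not count. It is 17.6%, 27.0% or 46.4% if they count and add 5%, 10% or 20%.

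**4. What these figures compare.** The s = 0 row applies only if short cytopenias are kept out of the escalation decision. The escalation rule as printed lets them in whatever line 5 means. Editing line 5 alone would therefore move none of these probabilities.

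**The case against.** A reader might infer that line 5 cancels the duration and fever limits, so that every short cytopenia is miscounted as dose limiting. The documents do not support that, for three reasons.

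- *Other* more naturally means types of toxicity not already listed. Neutropenia and thrombocytopenia have lines of their own; lymphopenia, AST, ALT and bilirubin do not, which is reason enough to exclude them by name. The naming of lymphopenia therefore does not show that line 5 was meant to take in the other cytopenias.
- The wider reading would leave lines 2, 3 and 4 without work to do, and a reading that gives each line an effect is preferable.
- The list defines serious adverse events. Dose-limiting status comes from the sentence after it. The fever condition belongs to neutropenic infection only, and the thrombocytopenia limit to grade 3 only.

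These points stand, and they reduce the matter within the list to an ambiguity. They do not remove it. The list is introduced as one of events, and it splits thrombocytopenia by grade and duration, so *other events* remains a possible reading.

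Three further objections concern size. The expected common effects under Safety profile include no cytopenia, patients with low leukocytes or platelets are excluded, and laboratory tests during follow-up are weekly, so short cytopenias may be rare or unseen. The probabilities rest on assumed rates. The independent data monitoring committee must review the toxicity data before the next cohort opens. All three are fair. Committee review lowers the risk of a mechanical miscount, but the committee still has no single definition to apply.

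**Conclusion.** The point holds as an inconsistency in definition. Three places bear on whether a short or afebrile cytopenia is dose limiting: the catch-all, which is ambiguous; the closing sentence, which does not name its lines; and the escalation rule, which counts every toxicity of grade 3 or higher. The firmest conflict is between the escalation rule and the limits in the list. The ambiguity in the catch-all matters in addition, because an escalation rule that was simply redirected to the list would inherit it.

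The size cannot be fixed from the documents. With 3 to 6 patients per cohort, one patient's classification can decide between escalation, expansion and stopping. The rise from 11% to 19%, 33% or 56% shows sensitivity under assumed constant and independent risks; it is not a forecast. It arises through the escalation rule, not through the wording of the catch-all alone. The matter should be corrected because it concerns the event behind the primary objective and the correction is cheap.

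**What to change.** Reconcile the passages so that each cytopenia has one rule:

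1. **Catch-all.** Either state that neutropenia and thrombocytopenia count only as defined in the lines above it, or remove the duration and fever qualifiers from those lines. The choice is the sponsor's, and this review takes no position on it.
2. **Closing sentence.** Name the lines of the list that are dose limiting.
3. **Escalation rule.** Let expansion, escalation and stopping refer to that same list. This step is essential, since without it the first two do not affect any dose decision.

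The cost is a clause or a sentence in each of three places, settled before the first cohort review and shared with the monitoring committee. No added patients or data are needed, and the sample size stays at 15 to 24.
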